## Methods

### Study design

This protocol describes a multicenter, prospective, observational cohort study on diverticular disease. The DDR Trial is open to participation by all tertiary-care hospitals. The DDR Trial aims to investigate short-term postoperative and long-term quality of life outcomes in patients undergoing surgery or medical treatments for diverticular disease. The primary outcome is the quality of life assessment at 12-month in patients with diverticular disease according to the Gastrointestinal Quality of Life index (GIQLI) [19]. The secondary outcome is 30-day postoperative outcomes according to the Clavien-Dindo classification [20].

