Follow-up will be done yearly assessing patient status, time to recurrence, symptoms, medication, consideration of surgical intervention, and quality of life (CRF7). Quality of life will be evaluated according to the Gastrointestinal Quality of Life index (GIQLI) [19]. The GIQLI is a 36-item patient reported outcomes instrument designed to assess GI-specific health-related quality of life in clinical practice and clinical trials of patients with GI disorders. It has five domains (GI symptoms, emotion, physical function, social function and medical treatment) and subscores range from 0–4 while the total score range from 0–144. Higher scores mean better GI health-related quality of life [19]. In addition, Female Sexual Function Index (FSFI) [24], International Consultation on Incontinence Questionnaire (ICIQ) [25], International Index of Erectile Function (IIEF) [26,27], and International Prostate Symptom Score (IPSS) [28], will be used, as appropriate.

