### Data analysis plan

Data analysis will primarily explore the quality of life in patients with DD after different treatments. Secondly, we aim to evaluate surgical management and short-term 30-day postoperative outcomes. We will explore baseline covariants that may identify clinical parameters correlating with favorable outcomes or be predictive of failure in patients undergoing different treatments for DD. Furthermore, we will evaluate recurrence, successive presentations (health utilization), and mortality rates. No personal or hospital-specific comparisons will be performed. The results of the DDR Trial will be reported according to the STROBE statement [31].

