#### Statistical analysis

Categorical data will be summarized by frequencies and percentages, and compared using the chi-squared test. Continuous data will be summarized by mean and standard deviation (normally distributed data) or median and interquartile range (non-normally distributed data), and will be compared using the t-test or ANOVA (normally distributed data) and Mann-Whitney U test or Kruskal-Wallis test (non-normally distributed data), as appropriate. Logistic regression models will be developed to examine the relationship between outcomes and covariates. Survival analysis (e.g., Kaplan-Meier) will be used to study the time-to-event. A two-sided p-value <0.05 will be considered statistically significant.

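### The only covariate model named is logistic regression, for outcomes in general, although the primary outcome is the 0–144 GIQLI total and no GIQLI cut is fixed

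*Protocol article*

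**What the plan says.** Study design in the protocol article sets the endpoint: "The primary outcome is the quality of life assessment at 12-month in patients with diverticular disease", measured by GIQLI. Study variables describes GIQLI as a 36-item instrument whose "subscores range from 0–4 while the total score range from 0–144", higher being better. The same section says that quality of life is also collected at baseline.

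Data analysis plan puts quality of life after different treatments first, then 30-day surgical outcomes, and then states the predictor aim: "We will explore baseline covariants that may identify clinical parameters correlating with favorable outcomes or be predictive of failure". Neither a favorable outcome nor failure is given a GIQLI value anywhere in the article.

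Statistical analysis assigns methods by type of data:

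- Categorical data get the chi-squared test.
- Continuous data "will be compared using the t-test or ANOVA (normally distributed data) and Mann-Whitney U test or Kruskal-Wallis test (non-normally distributed data), as appropriate".
- For time to event, "Survival analysis (e.g., Kaplan-Meier) will be used to study the time-to-event".
- For covariates there is one sentence: "Logistic regression models will be developed to examine the relationship between outcomes and covariates".

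**The concern.** The unadjusted methods are chosen by data type, but the covariate step is not. It names a single model for outcomes without qualification, and the primary outcome is one of them. Logistic regression in its ordinary sense takes a yes/no outcome. A reader who applied the sentence to GIQLI, alongside the two-way language of the predictor aim, would have to choose a threshold that the article does not give.

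Three things would be at stake in the covariate analyses of GIQLI:

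- Power to find predictors would fall.
- Patients just either side of the cut would be treated as opposites.
- If the cut were chosen after the data were seen, the list of predictors could depend on that choice.

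**Working it through.** **No figure to reproduce.** The article states no sample size, power, standard deviation, effect size or GIQLI cut. What follows sizes a conditional loss.

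**Inputs from the article.** Total score 0–144 (Study variables); two-sided 5% significance (Statistical analysis).

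**Assumed inputs.** A roughly normal score, a small covariate effect, a cut placing a share p of patients on one side, and 80% power on the full score as a reference point.

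**Step 1: information kept after a binary cut.** Relative efficiency is E = φ(z_p)² / [p(1−p)], where φ is the standard normal density.

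- p = 0.5: 0.3989² / 0.25 = 0.637, so 36% is lost.
- p = 0.3: 0.3477² / 0.21 = 0.576, so 42% is lost.
- p = 0.2: 0.2800² / 0.16 = 0.490, so 51% is lost.
- p = 0.1: 0.1755² / 0.09 = 0.342, so 66% is lost.

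**Step 2: effect on power.** A predictor with 80% power on the full score has an expected test statistic of 1.96 + 0.842 = 2.802. After the cut this is multiplied by √E, so power = Φ(2.802·√E − 1.96).

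| Cut | √E | 2.802·√E − 1.96 | Power |
|---|---|---|---|
| 50/50 | 0.798 | 0.28 | 61% |
| 70/30 | 0.759 | 0.17 | 57% |
| 80/20 | 0.700 | 0.00 | 50% |
| 90/10 | 0.585 | −0.32 | 37% |

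**Step 3: cross-check with an explicit two-group comparison.** Assume a standardised difference of 0.3. On the full score, n = 2 × 2.802² / 0.3² gives 175 per group for 80% power. A cut at the midpoint turns the difference into 0.56 versus 0.44, which needs 275 per group, and 175/275 = 0.64. Cuts at 70/30, 80/20 and 90/10 need 305, 360 and 518 per group. With 175 per group, power is 61%, 56%, 50% and 37% across the four cuts, in line with Step 2.

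**Step 4: how far the result depends on the assumptions.**

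- *Ordinal model.* Under normality, proportional odds on the uncut score has efficiency of about 3/π = 0.955, a loss of about 5%. With five equal ordered categories efficiency is 0.888, a loss of about 11%.
- *Shape of the score.* For a heavier-tailed, logistic-shaped score, E = p(1−p)·π²/3. That is 0.822 at the median (18% lost) and 0.296 at 90/10 (70% lost).
- *More extreme cut.* For a normal score cut at 95/5, E = 0.224, so 78% is lost.

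**The case against.** The strongest reply is that the article never says GIQLI will be cut. Its Introduction ties the search for favorable clinical parameters to recurrence, use of health care and death, without listing GIQLI. Recurrence and death are events, and 30-day complications suit a logistic model. The continuous-data tests use the uncut score. The covariate sentence does not say binary, and ordinal logistic regression would satisfy it. The type of model and any threshold are also details that a condensed article may leave to the full protocol or analysis plan, and the predictor work is exploratory.

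Much of this stands. A reader might infer that the plan requires GIQLI to be split into good and bad, that every other model is excluded, or that a third to two thirds of the information is thrown away. The documents do not support any of these. No split is announced, naming one model does not rule out others, an ordinal form keeps about 95% of the information, and the loss figures rest on a distribution and a cut that the article does not give. Nor does the point reach the unadjusted treatment comparisons.

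The mismatch itself remains. Data analysis plan states the predictor aim directly after quality of life and surgical outcomes, and adds recurrence, later presentations and mortality afterwards as a further item, so the aim is not confined to those events there. The article also does not defer the choice of model. It makes one, for outcomes in general, having just separated continuous from categorical data for the unadjusted tests.

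**Conclusion.** The point holds as a mismatch between the named covariate model and the scale of the primary outcome, with no GIQLI cut fixed should a binary form be meant. It is confined to covariate analyses of GIQLI.

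Its size depends on what is actually done. Linear regression on the full score is the reference, with no loss. Proportional odds on the full score loses about 5% under normality. A binary cut of a roughly normal score loses 36% at 50/50 and 66% at 90/10. The distribution, the cut and the 80% starting power are assumptions made here, so these figures show what a split would cost and are not a known defect of the plan. The dependence of results on a cut chosen late does not rest on normality.

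**What to change.** Amend the covariate sentence in Statistical analysis along these lines:

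> Covariate analyses of 12-month GIQLI will use linear regression on the full score, with baseline GIQLI as a covariate, or a proportional-odds model if the score is strongly skewed. Binary logistic regression will be used for outcomes that are binary in a fixed window, such as 30-day complications.

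If a binary GIQLI is wanted as well, fix and justify the cut before the data are examined.

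The cost is a change of analysis wording. Baseline quality of life is already collected, so no form or visit changes. Under the linear model, results for GIQLI are reported in points instead of odds ratios.

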## Abstract

**Highlights:**

## Introduction

Diverticular Disease (DD) is defined as clinically significant and symptomatic colonic diverticulosis and includes diverticular bleeding, diverticulitis, and Symptomatic Uncomplicated Diverticular Disease (SUDD) [1]. DD prevalence increases significantly with age, ranging from 10–20% in those younger than 40 years up to 50 to 70% in those older than 70–80 years [2,3]. While diverticulitis occurs in around 5% (1.7% complicated) of patients with diverticulosis [4], admission rate is steadily increasing overall and at a higher rate in younger patients [5]. Indeed, risk factors for DD such as obesity, diet low in fiber, lack of exercise, smoking, and aging of population are increasing. Along with the different clinical presentations and populations affected by DD, diagnosis and treatments have consistently changed. To standardize the treatments, several classifications have been proposed through the years, and several algorithms developed focusing on clinical features and patient’s quality of life more than anatomical and pathological landmarks [1,2,6,7,8]. Moreover, different surgical treatments have been proposed [8,9,10,11,12], while the surgical approach has been shifting to a minimally invasive approach even in the emergency setting [13,14]. Indeed, population, natural history, presentation, severity, and treatment for DD are heterogeneous, and optimal care for patients with DD needs high-quality evidence from large cohort studies [15]. Initial experiences of registry on DD recently appeared in the literature [16,17,18], suggesting the genesis of networks dedicated to DD as the best feasible way to strengthen clinical evidence. However, very few prospective cohort studies explore the outcomes between the different presentations and treatments for DD.

The Diverticular Disease Registry (DDR Trial), on behalf of the Advanced International Mini-Invasive Surgery (AIMS) academy clinical research network, will investigate both short-term 30-day postoperative outcomes and 12-months quality of life assessment in patients with DD. All different surgical and medical treatments will be explored to define the best management for each different presentation of DD. In addition, clinical parameters correlating with favorable outcomes in patients undergoing surgery or medical treatment for DD will be considered according to recurrence, health utilization, and mortality rates.

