#### Inclusion criteria

All adult patients (≥18 years old) with colonic DD will be included. DD is defined as clinically significant and symptomatic colonic diverticulosis and includes diverticular bleeding, diverticulitis, and Symptomatic Uncomplicated Diverticular Disease (SUDD). Symptoms include but are not limited to fever, alternating bowel habits, pain, diverticular bleeding, and dysuria. The presence of colonic diverticulosis needs to be confirmed by imaging or during emergency surgery and/or by pathological diagnosis. After obtaining written informed consent, either patient presenting in an outpatient or emergency department will be enrolled. According to the European Society of Coloproctology guidelines [1], a colonoscopy confirming DD will be required during the follow-up or before surgical treatment, if feasible.

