### Study variables

The DDR Trial’s variables will include patient baseline, presentation, diagnosis, treatment, and follow-up of patients enrolled, as reported in the CRF. Study variables will be documented for every patient’s presentations and treatments.

Patients enrollment and baseline will be recorded during the first surgical visit, together with a complete clinical examination. In particular, anthropometrics, habits, comorbidity, relevant medications, and baseline quality of life will be collected and categorized (CRF1- CRF2). Charlson comorbidity score adjusted for age will be calculated for every patient [21]. Patients older than 70 years old will be assessed for frailty risk using the modified Frailty Index described by Robinson et al. [22].

Patients and disease presentations are collected according to two different settings (from the emergency room or ambulatory/outpatient clinic). Symptoms, previous presentation, diagnosis, and treatments, need for admission, and treatment will be recorded (CRF3).

Instrumental diagnostic data from colonoscopy, abdominal computerized tomography (CT) and virtual CT colonoscopy be collected (CRF4).

Surgical pre- and intraoperative details will be recorded in the DDR Trial both for emergency procedures and for elective procedures, such as surgical setting, surgical procedure, resection, peritoneal lavage, laparoscopy, operative time, estimated blood loss, conversion, type of mesenteric artery ligation, stapler used and other technical aspects (CRF5). 30-day postoperative complications will be reported and graded according to the Clavien-Dindo classification [20]. Length of stay and post-discharge complications will be evaluated and recorded. Application of Enhanced Recovery After Surgery (ERAS) protocols will be considered valid if only at least 80% of the designed colorectal items will be satisfied [23].

Specimen length, the presence of microscopic and macroscopic abscesses, Crohn’s-like reaction, lymphocyte infiltration, and unknown cancer will be obtained by the pathology report for patients who underwent surgical resection (CRF6).

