As previously mentioned, other similar experiences are now ongoing in the medical panorama. Although conceived as snapshot studies, the REMAD registry has produced consistent and valuable data for clinical practice from patient follow-up [16,17], and the DAMASCUS study will investigate current practice and outcomes worldwide [18]. Differently, after the primary study at 12-month, the DDR Trial will have a recruitment period of 5 years with the aim of collecting long-term prospective outcomes for both surgical and medical treatment from a large cohort of patients.

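### If Kaplan-Meier is applied to time to recurrence with deaths censored, long-term recurrence risk is overstated; cumulative incidence should be named instead (low severity)

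*Protocol article*

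**What the plan says.** The Statistical analysis section has one sentence on event times: "Survival analysis (e.g., Kaplan-Meier) will be used to study the time-to-event". It does not say which event is meant, when patients are censored, or how death is treated.

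Other sections of the article show where the sentence is likely to apply:

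- Study variables describes the annual visits: "Follow-up will be done yearly assessing patient status, time to recurrence, symptoms, medication, consideration of surgical intervention, and quality of life (CRF7"). Recurrence is the only item there expressed as a time to an event. Vital status and possible surgery are recorded at the same visits.
- The Data analysis plan section sets recurrence and death side by side as further outcomes: "Furthermore, we will evaluate recurrence, successive presentations (health utilization), and mortality rates".
- The Discussion explains the long recruitment period "with the aim of collecting long-term prospective outcomes for both surgical and medical treatment from a large cohort of patients".
- On age, the Introduction notes that "DD prevalence increases significantly with age", but eligibility is broad: "All adult patients (≥18 years old) with colonic DD will be included". Frailty is assessed only in those over 70.

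The text shown does not mention competing risks or cumulative incidence, and gives no recurrence, death or resection rate.

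**The concern.** Kaplan-Meier treats a censored patient as someone who could still have the event at the same rate as those who remain under observation. A patient who has died cannot have a recurrence. If deaths are censored, 1-KM describes a hypothetical population in which nobody dies. It is not the proportion of patients who will have a recurrence, and it can never be smaller than that proportion.

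Absolute long-term recurrence is a figure that clinicians would use when weighing surgery against conservative care, and the Discussion presents the registry as evidence for that decision. Treatment is not randomised, so mortality may differ between the treatment groups. The overstatement would then differ between them too, and the comparison of absolute risks would be distorted.

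Later resection in a conservatively treated patient raises a separate question. Ongoing disease is a likely reason for resection, so simply censoring at resection is likely to be informative.

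**Working it through.** **Inputs.** The article states no event rate and no maximum follow-up, so there is no figure of its own to reproduce. All rates below are assumptions: recurrence hazard r = 0.06 per year; death hazard d = 0.01, 0.02, 0.05 and 0.08 per year; both constant and independent. The 5-year horizon is also an assumption. It matches the period for which, under Ethics, the link between patient and study code is kept.

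**Formulas.**

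- With deaths censored: 1-KM = 1 − exp(−r·t)
- Cumulative incidence with death as a competing event: CIF = r/(r+d) × [1 − exp(−(r+d)·t)]

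**At 5 years.** 1-KM = 1 − exp(−0.30) = 25.9%, whatever the death rate.

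| Death per year | CIF calculation | CIF | Gap (points) | 1-KM / CIF |
|---|---|---|---|---|
| 1% | 0.06/0.07 × (1 − exp(−0.35)) | 25.3% | 0.6 | 1.02 |
| 2% | 0.06/0.08 × (1 − exp(−0.40)) | 24.7% | 1.2 | 1.05 |
| 5% | 0.06/0.11 × (1 − exp(−0.55)) | 23.1% | 2.8 | 1.12 |
| 8% | 0.06/0.14 × (1 − exp(−0.70)) | 21.6% | 4.3 | 1.20 |

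**At 12 months.** 1-KM = 1 − exp(−0.06) = 5.8%. With death at 8% per year, CIF = 0.06/0.14 × (1 − exp(−0.14)) = 5.6%, a gap of about 0.2 points. Lower death rates give less.

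**Sensitivity to the recurrence rate.** With death at 8% per year, the 5-year gap is 1.6 points for r = 0.02 (9.5% against 7.9%) and 5.4 points for r = 0.08 (33.0% against 27.5%; the difference is taken before rounding). With death at 1% per year, the gaps are 0.2 and 0.8 points.

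**Unequal effect.** Take two groups with the same recurrence hazard, 6% per year, and death at 2% in one and 5% in the other. Kaplan-Meier gives 25.9% in both. The cumulative incidences are 24.7% and 23.1%, so the overstatement is 1.2 points in one group and 2.8 in the other.

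**Resection.** If resection at 5% per year (assumed) is added as a further competing event, the 5-year CIF falls to 0.06/0.16 × (1 − exp(−0.80)) = 20.7% with death at 5%, and to 0.06/0.19 × (1 − exp(−0.95)) = 19.4% with death at 8%. These figures hold only if resection is defined as a competing event and is independent of recurrence risk. The article establishes neither, so they are not part of the conclusion.

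**The case against.** The strongest objection is that the sentence does not do what is criticised. Kaplan-Meier is an example, no endpoint is attached, and mortality, for which Kaplan-Meier is the right estimator, is one of the outcomes. Nothing says that deaths will be censored. The article condenses a fuller protocol, the analysis plan is not shown, and the handling of competing events for a further outcome is often settled there. All of this stands. It makes the point conditional and lowers its severity. It does not remove it: the article does name one time-to-event estimator, and recurrence is the natural candidate for it.

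A reader might also infer three stronger statements that the documents do not support.

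- **That long-term recurrence will be overstated because this is an elderly cohort.** All adults are eligible and no age distribution is given. Patients over 70 are a subgroup, and the Introduction says that admissions are rising faster in younger patients. Nor does anything show that medically managed patients are older or die more often.
- **That later resection is a competing event like death and adds to the overstatement.** Resection does not make recurrence impossible, and the article defines neither recurrence nor follow-up after surgery. If the patients operated on are those at higher risk, censoring them would make Kaplan-Meier understate the risk of recurrence without surgery, which is the opposite direction.
- **That the overstatement reaches about a third.** A ratio of 25.9/19.4 = 1.34 needs death at 8% and resection at 5% per year together, with resection counted as competing.

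**Conclusion.** The point holds in conditional form. If Kaplan-Meier is applied to recurrence with deaths censored, 1-KM is biased upward as an estimate of absolute recurrence risk, and the bias differs between treatment groups if their mortality differs. The direction is certain; the size is not. With death alone and recurrence at 6% per year, the overstatement at 5 years runs from about 0.6 points (death 1% per year) to about 4.3 points (8% per year), and it is negligible at 12 months. These figures rest on assumed constant, independent hazards.

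Severity is low. The Study design section makes 12-month GIQLI the primary outcome and 30-day postoperative outcomes the secondary one, and neither is affected.

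**What to change.** In the Statistical analysis section, replace the general sentence with text to this effect:

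- Recurrence is defined, and its risk is reported as cumulative incidence (Aalen-Johansen) with death as a competing event.
- Treatments are compared on recurrence with cause-specific hazard models, with the covariates named. The article specifies no primary regression model from which they could be taken.
- Kaplan-Meier is kept for all-cause mortality. Show mortality beside recurrence, so that a lower recurrence risk caused by more deaths is not read as a benefit.
- The estimand for later resection in conservatively treated patients is stated: competing event, change of treatment, or part of a composite failure. Follow-up is not simply censored at resection.

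The resection choice needs thought. Counting resection as a competing event removes patients operated on for persistent disease from the recurrence figure, which could flatter conservative care.

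The cost is a few sentences and a little more analysis work with standard software. Patient status, time to recurrence and consideration of surgery are already follow-up items. Reported recurrence risks would be slightly lower.
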